
### Equipment

Certified NAATI-approved translators (Ethnolink, OPAL Translation Pty Ltd) will be used for the translation of the intervention written materials into the five (5) culturally appropriate languages predominantly spoken in the target geographical areas of interest (Chinese, Arabic, Hindi, Vietnamese, Hindi, and Punjabi), as described earlier.

Digital weight scales (Seca Clara 803) will be used for body weight measurement of participating children. Portable stadiometers (Charder HM200P Portstad) will be used for the measurement of height of participating children. Outcomes measures will be collected and recorded on a portable tablet computer (Lenovo Tab E7, Lenovo PC HK Limited, Bratislava, Slovakia).

### Sample size determination

A minimum sample size was calculated on the statistical power required to detect a difference in standardized BMIz score of 0.15 (SD:0.8) with 80% power and 5% significance level. Taking into account a 19% dropout at end of the intervention and an 11% dropout at follow-up as established in our pilot study, [17] the required sample size is 800 participants after accounting for clustering (i.e. 800 parent- or carer-child dyads) (400 in intervention and 400 in the control group).

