### Randomisation / group allocation

The trial will use a cluster RCT design with the primary unit of randomisation being postcode. Each of the 92 postcodes within the study areas will be allocated to an intervention or control arm according to a randomisation schedule generated by the trial biostatistician. The allocation ratio between the intervention arm and the control arm is 1:1.

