### Statistical analysis

Data on socio-demographics, anthropometry, general parenting, feeding-related parenting, child’s health and quality of life, physical activity and consumption of healthy foods, parents’ health knowledge and health and household costs will be collected. Child’s anthropometric measurements will be taken at baseline, at completion of the intervention and 12 months after completion of the intervention. Height and weight of the participating child will be used to calculate the BMIz score (primary outcome measure) [57, 58]. Cost per BMIz saved and incremental cost per quality-adjusted life-year gained will also be calculated (Incremental cost per quality-adjusted life-year gained at baseline, end of intervention and 12 months following intervention). Parents will respond to self-administered questionnaire on family functioning, feeding related parenting, physical activity and consumption of healthy foods of the participating child, parents’ health literacy, and family and household costs. The analysis will follow an intention-to-treat approach and with supplementary per protocol analysis. Research data will be analysed with Stata 16 [59]. The statistical analysis will use a modelling approach that aims to capture the profile of the intervention group compared to the control group and while accounting for potential unobserved differences between the intervention and control groups that (if not accounted for) could bias results. The models will evaluate the impact of the interventions over time by testing for an interaction between time and intervention group. This will be followed by multivariable linear models after adjusting for baseline characteristics and other variables (standard demographic variables such as age, sex, income, education, and SEIFA). Subgroup analysis will be undertaken for within-intervention group differences between English speaking and Non-English-speaking groups. Model assumptions will be checked and appropriate adjustments to the analysis made where necessary. A *p*-value <0.05 will be considered statistically significant. The cost-effectiveness analyses will be conducted to determine incremental cost per quality adjusted life year gained by comparing the direct costs and outcomes of behavioural parenting and lifestyle program over usual care from a health care perspective at completion of the intervention and at 12 months post-intervention. The within-trial analysis will adopt a micro-costing approach to calculate the costs of resources used to implement the intervention, including training, staff and travel costs; family or household costs (resources related to food shopping and activities); and health care resources. One of the aims of the project is to undertake economic evaluation to evaluate the effectiveness of the proposed intervention for parents or carers from disadvantaged backgrounds, in preventing unhealthy weight gain in children aged 5 to 11 years living in the same household. This requires data linkage to Medicare funded services and dispensing of subsidised pharmaceuticals to capture total health care expenditure and out-of-pocket costs (Services Australia RMS1190). All analyses will be adjusted for clustering and all participant data will be de-identified prior to analysis.

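### The sample size of 800 does not follow from its stated inputs: a two-sided unadjusted comparison needs 894 before the dropout and clustering that 800 is said to include

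*Protocol article*

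**What the plan says.** Under Sample size determination, the protocol article sets out to "detect a difference in standardized BMIz score of 0.15 (SD:0.8) with 80% power and 5% significance level". It continues: "Taking into account a 19% dropout at end of the intervention and an 11% dropout at follow-up", with both rates attributed to the pilot study, and concludes that "the required sample size is 800 participants after accounting for clustering", split as "400 in intervention and 400 in the control group".

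Under Randomisation / group allocation, 92 postcodes are the units randomised, and "The allocation ratio between the intervention arm and the control arm is 1:1".

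Under Statistical analysis, the decision rule is "A *p*-value <0.05 will be considered statistically significant". The models test a time-by-group interaction and are followed by linear models that adjust for baseline characteristics and demographic variables. All analyses allow for clustering.

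The sample-size paragraph does not give sidedness, an ICC or design effect, or a baseline/follow-up correlation. It does not say whether the two dropout rates add up, and it does not describe the SD of 0.8 as a residual or change-score SD.

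**The concern.** Dropout and clustering can only raise a required sample size. Under the usual two-sided convention, the number needed before either allowance is already above the number said to include both. The printed figures therefore conflict with one another. This differs from an ICC left out for brevity, because any ICC of zero or more widens the gap.

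BMIz is the primary outcome, and this paragraph is the article's only justification for the trial's size. If the trial finds no effect, readers will set that result against a claim of 80% power for 0.15. They need to know whether the claim can be supported, and under which analysis.

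**Working it through.** **Inputs from the protocol article.** Difference 0.15, SD 0.8, power 80%, level 5%, dropout 19% and 11%, total 800 (Sample size determination); 92 postcodes, 1:1 (Randomisation / group allocation).

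**Assumptions made here.** Two-sided test unless stated otherwise; ICC 0.01 to 0.05; all 92 postcodes contribute equally; dropout either 19% in total or 19% followed by 11%.

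**1. Trying to reproduce 800, two-sided.**

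n per arm = 2 × (1.960 + 0.8416)² × 0.8² / 0.15² = 446.5, so 447 per arm and 894 in total. (A t-test calculation gives 448 per arm.)

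- 11% loss only: 894 / 0.89 ≈ 1,005
- 19% loss only: 894 / 0.81 ≈ 1,104
- 19% then 11%: 894 / (0.81 × 0.89) = 894 / 0.7209 ≈ 1,240

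None of these includes clustering, and all exceed 800.

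**2. Trying to reproduce 800, one-sided.**

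The total is 703.4, or 704 rounded up, which is below 800.

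- 19% loss only: 703.4 / 0.81 = 868.4, so 869
- 19% then 11%: 703.4 / 0.7209 = 975.7, so 976
- 11% loss only: about 792. This is close to 800, but it leaves out the 19% loss and all of the clustering that the text says are included.

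No calculation using all the stated inputs returns 800.

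**3. Power of 800 on the stated inputs (two-sided, unadjusted, no clustering).**

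Power = Φ(0.15 / (0.8 × √(2/n)) − 1.960), with n per arm.

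| Analysed | n per arm | Power | Difference detectable at 80% |
|---|---|---|---|
| 800, no loss | 400 | 75.5% | 0.159 |
| 648, 19% in total | 324 | 66.5% | 0.176 |
| 577, 19% then 11% | 288.4 | 61.5% | 0.187 |

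The detectable difference is 2.8016 × 0.8 × √(2/n).

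**4. Adding clustering (ICC assumed).**

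Design effect = 1 + (m − 1) × ICC, where m is the number analysed per postcode: 648 / 92 = 7.04, or 577 / 92 = 6.27.

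- 648 analysed, ICC 0.01: design effect 1.06, power 64%, detectable difference 0.176 × √1.06 ≈ 0.18
- 648 analysed, ICC 0.05: design effect 1.30, power 55%
- 577 analysed, ICC 0.01: design effect 1.05, power 59%
- 577 analysed, ICC 0.05: design effect 1.26, power 52%, detectable difference 0.187 × √1.26 ≈ 0.21

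**5. What baseline adjustment would have to supply.**

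Adjusting for baseline BMIz multiplies the required n by (1 − r²), where r is the baseline/follow-up correlation. With 577 completers, 80% power needs r = √(1 − (288.4 / design effect) / 446.5).

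- No clustering: √(1 − 0.646) ≈ 0.60
- ICC 0.05: √(1 − 0.511) ≈ 0.70

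**The case against.** The strongest objection is that the unadjusted power figures describe an analysis that the protocol does not plan. BMIz is measured at 0, 10 and 60 weeks, and the Statistical analysis section plans time-by-group and baseline-adjusted models, which use the child's own baseline. With 577 completers, baseline-adjusted power for assumed correlations of 0.5, 0.6, 0.7 and 0.8 is 74%, 80%, 88% and 96% with no clustering, and 64%, 71%, 80% and 92% with a design effect of 1.26. This stands. A reader might infer that the trial has little better than even odds of detecting 0.15, but the documents do not show that. The low end needs an unadjusted analysis, sequential losses and an ICC of 0.05, none of which the article states.

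The objection does not rescue the paragraph. It gives no correlation, and the analysis section speaks of baseline characteristics without naming baseline BMIz or tying the power claim to any model. If 0.8 were already a residual or change-score SD, the gain from baseline would be inside the inputs and 894 would stand.

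Two further objections limit the wording:

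- **Sidedness is not stated.** A reader might infer that 800 falls short before inflation on any reading. That is true two-sided but not one-sided, where 704 suffices before losses.
- **The dropout rates may not be sequential.** If 19% is the total loss, 648 are analysed and unadjusted power is 66.5%, not 61.5%.

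Finally, a journal article condenses its source, and the ICC, correlation and sidedness may be in the full protocol. Their absence alone is therefore not the point. The point is that the printed inputs and the printed total disagree.

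**Conclusion.** The point holds as a mismatch between stated inputs and stated result. The two-sided unadjusted requirement before inflation exceeds 800 by 94 (894 − 800). After the stated losses the shortfall is about 304 to 440 (1,104 − 800 and 1,240 − 800) before any clustering. Neither choice of sidedness gives 800 once all the stated allowances are applied. This conclusion does not depend on the assumed ICC.

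The power figures are conditional. About 61–67% assumes an unadjusted single-timepoint comparison with no clustering. About 52–64%, and the detectable difference of about 0.18–0.21, also rest on the assumed ICC range and equal postcode sizes. Whether the trial is actually underpowered cannot be settled from the article. It turns on whether the primary model adjusts for baseline BMIz, and on whether the correlation reaches about 0.60 to 0.70 if losses are sequential. What is established is that the 80% claim is not supported by the figures printed beside it.

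**What to change.** Correct the paragraph without enrolling more families. Recompute and restate the power, or the detectable difference, for 800 recruits under the analysis that will be primary. State the sidedness, how the two dropout rates combine, the ICC and the cluster size.

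- If 800 relied on baseline adjustment, state the assumed correlation and name the model adjusted for baseline BMIz and for clustering as the primary analysis, so that the power claim and the analysis match.
- If it did not, state the lower power or the larger detectable difference, and label it as unadjusted. The unadjusted figures should not be entered without that label, because they could mislead in the other direction once baseline is used.

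The cost is one recalculation and one reworded paragraph, and possibly a less favourable stated figure.

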### Randomisation / group allocation

The trial will use a cluster RCT design with the primary unit of randomisation being postcode. Each of the 92 postcodes within the study areas will be allocated to an intervention or control arm according to a randomisation schedule generated by the trial biostatistician. The allocation ratio between the intervention arm and the control arm is 1:1.

### Blinding

All bilingual field workers will be blinded to randomisation and will therefore have no knowledge of which group (intervention or control) the participating parent- or carer-child dyad has been allocated to. Group facilitators are unable to be blinded to randomisation given the nature of the intervention but will only be assigned after baseline data collection has been completed. Furthermore, they will take no part in data collection and will only be involved in the delivery of their designated intervention modules. Research staff will not take part in data collection.

### Intervention

Consenting participants nested in the postcodes randomised to the intervention arm will receive the intervention as soon as possible after registration. The Strong Families program (the intervention) will be delivered in two stages: A 6-week group program consisting of 6 x 90-minute online sessions covering both healthy lifestyle and parenting modules. The online sessions will be facilitated by bilingual group facilitators with backgrounds in nutrition, dietetics, psychology or social sciences. The modules are designed to provide participants with new knowledge about healthy eating and physical activity (healthy lifestyle modules) and then teach them skills required to effectively implement this knowledge (parenting modules). Then, approximately 3 months after the weekly sessions, participants will attend 2 x 45-minute online booster sessions. The booster sessions are designed to reinforce and enhance the knowledge and skill development acquired in the weekly sessions. These sessions are also intended to allow participants to evaluate the family environment and troubleshoot any challenging areas. Sessions focus on establishing a welcoming and safe environment, and active learning approaches that maximise engagement in knowledge building of healthy habits, making healthy choices, building stronger families and positive family functioning as well as helpful communication strategies that are sensitive to culturally diverse families living in Australia.

The first three (1-3) modules will focus on creating healthy lifestyle choices as a family but particularly in reference to the participating child. This includes concepts such as reducing screen time and sedentary behaviours, making healthy food choices and increasing physical activity. The second three (4-6) modules focus on strengthening the family dynamic through parenting advice and guidance. Specifically, topics discussed include physical, emotional and social development of children, clear and effective boundaries and communication, understanding behaviour and consequences, and managing emotions. The two booster sessions will be revisions of materials previously discussed in the modules and the ensure understanding. Booster A will revise healthy lifestyles and review understanding of healthy food and lifestyle choices. Booster B will review parenting messages covered and provide guidance on maintaining progress in parental decision-making for a stronger family dynamic.

A detailed outline of each module and booster session is presented in 1. Group facilitators will be qualified bilingual health professionals such as dieticians, psychologists, social workers, counsellors; or bilingual and bicultural workers with previous experience in domains such as family support, community health education and health promotion. They will receive all materials to deliver the intervention from the research team, as well as a detailed instruction manual. All group facilitating staff were required to undergo appropriate recruitment and interview processes prior to employment.

**Table 1 Tab1:** Program Content of the ‘Strong Families Trial’ intervention

Type of Session	Session Number	Module Title	Objectives	Key Messages	Activities
Healthy Lifestyle Modules	Module 1	Building Healthy Habits	• Welcome participants, provide an opportunity for introductions and explore participant expectations and motivations for the program. • To promote a safe and supportive environment with which participants can actively engage. • To orient participants to the program. • To define key concepts. • Introduce the key healthy lifestyle messages. • To promote healthy drinking habits in children. • To promote physical activity as a part of a healthy lifestyle. • To encourage a reduction in sedentary behaviours. • Promote the importance of sufficient sleep each day for children.	• Strong families can be healthy together by following healthy lifestyle habits every day. • Choose water as a drink. • Be active every day for at least 60 mins. • Decrease screen time to move more and sit less. • Sleep plays an important role in your child’s health.	1.1 Welcome & introductions • Welcome • Session overview • Activity 1: Getting to know each other • Our group rules 1.2 Strong families • Program structure • Strong, healthy families • Healthy lifestyle habits 1.3 Choose water as a drink • Drink water instead of soft drink, juice or cordial • Activity 2: How much sugar • Tips for kids to drink more water 1.4 Getting active each day • Activity 3: Shake it out • Getting active every day • Active families 1.5 Switch off screens • Healthy screen use • Managing screen time 1.6 Sleep • Get enough sleep • Healthy sleep habits 1.7 Wrap-up • Key messages • Take-home activities • Questions • Feedback
	Module 2	Healthy Eating Every Day	• Provide an overview of the session and recap key messages from previous session. • Introduce participants to concept of ‘everyday’ foods and ‘sometimes’ foods using the Australian Guide to Healthy Eating (AGHE) and the five food groups. • Highlight the main nutrients & portion sizes for each of the five ‘everyday’ food groups and promote the benefits of healthy eating. • Increase participants understanding that ‘sometimes’ foods should be limited as they are high in fat, salt & sugar. • Introduce positive parenting feeding practices to promote development of healthy eating habits. • Encourage participants to enjoy breakfast each day. • Promote the importance of a healthy lunch box and snack choices and encourage increased intake of fruit & vegetables through these choices.	• Eat ‘everyday’ foods from the five food groups. • Increase ‘everyday’ foods and limit intake of ‘sometimes’ foods. • Children need a balance of foods and drinks for optimal growth and development. • Strong, healthy families enjoy eating together. • Breakfast is a great way to start the day. • Healthy lunchboxes and snacks contain ‘everyday foods’.	2.1 Introduction • Welcome • Module 2 overview • Recap - Module 1 2.2 Understanding healthy eating • ‘Everyday’ & ‘sometimes’ foods • Healthy fats • ‘Sometimes’ foods 2.3 Healthy eating habits • Building healthy eating habits 2.4 Good start to the day • Why is breakfast important? • What is in a healthy breakfast? • Breakfast helpers 2.5 Healthy lunch & snack habits • Healthy lunch & snack habits • Lunchbox & snack helpers • Activity 1: ‘Everyday’ lunches & snacks 2.6 Wrap-up • Key messages • Take-home activities • Questions • Feedback
	Module 3	Making Healthy Choices	• Allow participants to reflect on prior learning and to provide an overview of the module • To encourage limited intake of takeaway foods with high sugar, salt and fat through healthier food choices. • For parents to develop skills to enable them to modify recipes into healthier options. • For parents to be able to confidently read food labels & nutrition symbols to inform healthy choices. • To highlight that pre-planning can help make healthy food purchases and that healthy eating need not be expensive	• Simple swaps make favourite meals healthier • Understanding food labels can help you make healthy food choices at the supermarket. • Healthy food choices can be easy, convenient and affordable.	3.1 Introduction • Welcome • Module 3 overview • Recap - Module 2 3.2 Smart food swaps • Smart swaps for cooking • Healthier cooking methods • Healthy choices away from home • Activity 1: Recipe makeovers 3.3 Understanding food labels • How to read a food label • Nutrition information • Ingredients • Front of pack labelling • Activity 2: Food detectives 3.4 Smart supermarket choices • Isn’t healthy eating more expensive? • Healthy shopping habits • Supermarket savvy • Combating pester power 3.5 Wrap-up • Key messages • Take-home activities • Questions • Feedback
Parenting Modules	Module 4	Building Strong Families	• Provide an overview of the module and highlight the importance of family functioning on a family’s health • Explore participant’s expectations and experiences of becoming parents • Introduce the essential components of a strong family • Develop an understanding of the sequence of physical, emotional, social and cognitive changes that occur in children	• Our expectations and experiences of becoming a parent have been shaped by many things including our upbringing, values, family and cultural influences. • During childhood your child develops physically, emotionally, socially and cognitively. The relationship with their family plays an important role in supporting this development. • Children need strong families in order to thrive. • A strong family has emotional and physical security, lots of warmth, care and positive attention, firm, fair rules and boundaries, good communication and connections to others outside of the family.	4.1 Introduction • Welcome participants • Introduction to Module 4 4.2 Becoming a parent • Thoughts about becoming a parent 4.3 Essential components of a strong family • Strong Families • Activity 1: Bullseye 4.4 Understanding childhood development • Child developmental milestones 4.5 Wrap-up • Key messages • Take-home activities • Questions • Feedback
	Module 5	Praise, Rewards, Rules & Consequences	• Highlight the role of positive attention, praise and rewards in promoting good behaviour • Promote the importance of limit setting as a means to guide children’s behaviour • Develop an understanding of how to use consequences as a strategy to manage their children’s behaviour effectively.	• Family rules help create structure and can help guide children to understand what behaviours are okay and not okay. • The way that you respond to your child’s behaviour directly influences whether they are more or less likely to engage in the behaviour again. • Physical punishment (e.g. smacking) is not an effective way to help children to follow rules.	5.1 Introduction • Welcome • Introduction to Module 5 5.2 Promoting positive behaviour • The importance of praise • Tips for using praise • Rewards 5.3 Setting family rules • Family rules – what are they and why are they important? • Developing family rules • Following the rules: what to expect 5.4 Responding to children’s behaviour • Smacking- It is never okay • Using consequences effectively • Activity 1: How would I respond? 5.5 Wrap-up • Key messages • Take-home activities • Questions • Feedback
	Module 6	Improving Communication & Managing Emotions	• Explore challenges in communication and provide parents with tools for more effective communication. • Gain an understanding of how to support children to identify and manage their emotions effectively. • Equip parents with strategies to manage stress, highlighting the importance of self-care and support networks. • Explain the importance of chores.	• The way that we communicate with others has a significant impact on the quality of our relationship and on the outcomes of our interaction. • Emotions such as joy, sadness, fear, anger and disgust can occur daily. It is important to find healthy ways to express our emotions. • Stress is a normal part of life and is experienced by everyone from time to time. However, when stress is frequent or severe, it can impact on your quality of life and therefore it needs to be effectively managed. • Self-care can enhance your health and wellbeing and is vital in helping you care for others. • Assigning chores to family members can help reduce stress, while supporting children to develop essential life skills.	6.1 Introduction • Welcome • Introduction to Module 6 6.2 Improving family communication • Activity 1: Follow the instructions • Communication skills for your family • Teaching children how to communicate 6.3 Understanding emotions • The importance of understanding emotions • Activity 2: Identify the emotion • Helping children to deal with big emotions 6.4 Reducing stress • The basics of stress 6.5 Sharing the load • Chores for children 6.6 Wrap-up • Program recap • Activity 3: Creating a maintenance plan • Wrapping up and Next Steps • Feedback
Booster Sessions	Booster Session A	Healthy Lifestyles	• Welcome participants and introduce them to the first booster session. • Revise and assess participants understanding of the key messages of the healthy lifestyle modules. • Review implementation of Strong Families maintenance plan. • Ensure that participants have a thorough understanding of all key messages by addressing any questions and areas of concern.	• It is important to maintain the progress you have made in the Strong Families program to ensure that your family stays strong and healthy.	A.1 Introduction • Welcome • Introduction to Booster A A.2 Review of Healthy Lifestyle modules •Review of key messages A.3 Positive changes & ongoing challenges •Reflecting on learning A.4 Troubleshooting & wrap up •Troubleshooting •Feedback •Wrap up
	Booster Session B	Parenting	• Welcome participants and introduce them to the second booster session. • Revise and assess participants understanding of the key messages of the parenting modules. • Review implementation of Strong Families maintenance plan. • Ensure that participants have a thorough understanding of all key messages by addressing any questions and areas of concern.	• It is important to maintain the progress you have made in the Strong Families program to ensure that your family stays strong and healthy.	B.1 Introduction •Welcome •Introduction to Booster B B.2 Review of Parenting modules •Review of key messages B.3 Positive changes & ongoing challenges •Reflecting on learning B.4 Troubleshooting & wrap up •Troubleshooting •Feedback •Wrap up

